**Methods and analysis::**

This is a randomized, open-label, cetirizine-controlled clinical trial. A total of 30 AR patients who have signed informed consent forms will be recruited and randomly assigned to SCRT or cetirizine groups at a 1:1 ratio. The participants will visit the clinical research center every week and receive SCRT granules or cetirizine tablets. SCRT will be taken twice daily, cetirizine will be taken once daily, and treatment medication will be taken for 2 weeks. Data will be collected at baseline, at week 2, and at week 4 after random allocation. The primary outcome will be the mean change in the total nasal symptom score from baseline to week 2. Secondary outcome measures will include the mini Rhinoconjunctivitis Quality of Life Questionnaire and total serum immunoglobulin E. To assess the safety of SCRT, a liver and renal function test will be conducted before and after treatment, and the participants will be asked about any occurrence of adverse events at every visit. The recruitment rate, completion rate, and medication adherence will also be calculated to assess feasibility.

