#### Primary outcome

2.6.1

The primary outcome is the change in total nasal symptom score (TNSS). TNSS will be recorded in participants’ diaries every day before bedtime using a mobile application. A 4-point severity scale (no symptoms, 0; mild, 1; moderate, 2; and severe, 3) will be used.^[25]^ Using 4 weeks of TNSS scores, we will analyze the differences in the effects of SCRT and cetirizine, and the duration of the effects of each medication.

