### Sample size

2.10

No clinical trial has been conducted to evaluate the effects of SCRT on the TNSS for patients with AR. Therefore, we adapted the minimum number of subjects recommended for a preliminary study in the field of life sciences, 12 subjects in each group, for 24 subjects in total.^[30]^ Anticipating a dropout rate of 20%, the target of the recruitment is set to 15 subjects in each group, or 30 subjects in total.

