### Statistical analysis

2.11

An independent statistician who is blinded to the randomized allocation of participants will carry out the statistical analysis. Measured variables will be assessed using the full analysis set based on intention-to-treat principles, including all randomized participants who completing the trial without violating any of the exclusion criteria and for whom a complete set of data is available. The per-protocol analysis set will be used for the sensitivity analysis.

The demographic characteristics and baseline data of both groups will be summarized by means and standard deviations for the continuous variables, and frequencies and percentages will be presented for categorical variables. Baseline differences between groups will be assessed using independent *t* tests or Mann–Whitney *U* tests for continuous variables, and the chi-squared test or Fisher exact test for categorical variables. Differences in the primary and secondary outcomes will be analyzed using one-sided independent *t* tests. To demonstrate noninferiority, we will check whether the lower limit of the 2-sided 95% CI of the difference of the primary outcome between the 2 groups is greater than the noninferiority margin. The analysis will be presented as a difference with an associated 95% CI. To determine whether statistically significant differences exist between the groups, differences in the primary and secondary outcomes will be analyzed using a mixed effects model for repeated measurement. Subgroup analyses will also be conducted to investigate the difference in treatment effect according to the type of cold–heat pattern identification questionnaire, each symptoms of AR, and the results of Nasal Endoscopy Index. The level of significance will be set at 0.05 (2-tailed), and all analyses will be performed using SAS (V.9.4; SAS Institute).

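### The t test on change in TNSS, which sits with the noninferiority interval, is not adjusted for baseline TNSS and gives up precision at about 12 per arm

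*Protocol article*

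**What the plan says.** The abstract of the protocol article defines the endpoint: "The primary outcome will be the mean change in the total nasal symptom score from baseline to week 2". Section 2.6.1 also calls it a change in TNSS.

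Section 2.11 then makes four relevant statements:

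- **Baseline.** "Baseline differences between groups will be assessed using independent" t tests or Mann–Whitney tests for continuous variables, and chi-squared or Fisher tests for categorical ones. No action is attached to the results.
- **Outcomes.** "Differences in the primary and secondary outcomes will be analyzed using one-sided independent" t tests. No covariate is named.
- **Noninferiority.** The sentence directly after the t test sets this condition: "the lower limit of the 2-sided 95% CI of the difference of the primary outcome between the 2 groups is greater than the noninferiority margin".
- **Mixed model.** To look for statistically significant group differences, "differences in the primary and secondary outcomes will be analyzed using a mixed effects model for repeated measurement". The article does not list its fixed effects or covariates.

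Section 2.10 plans on "12 subjects in each group, for 24 subjects in total". Section 2.8 describes block randomisation and names no stratification by baseline TNSS.

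**The concern.** An independent t test has no place for a covariate, so no further detail elsewhere could make this comparison baseline-adjusted. Computing a change score is not the same as adjusting. It fixes the coefficient on baseline at 1, whereas the best coefficient, with equal SDs, is the baseline to week-2 correlation. Whenever that correlation is below 1, the change score over-corrects. The arm that happens to start worse then appears to improve more, whatever the treatments do.

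At stake are the width of the interval that carries the noninferiority decision and where its centre falls after an unlucky allocation. With so few patients, chance imbalance in baseline TNSS is common, and the description of randomisation names nothing that would limit it. Baseline TNSS is needed for the endpoint anyway, so adjusting for it requires no new data.

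**Working it through.** **Inputs from the article.** 12 evaluable patients per arm, dropout 20%, 15 randomised per arm (section 2.10); a change-score endpoint (abstract, section 2.6.1); a two-sided 95% CI (section 2.11).

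**Assumptions.** Baseline and week-2 TNSS have equal SD, and their correlation is r. The article gives neither, so r is shown over a range. All results are in units of that SD.

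**The plan's own figure.** 12 / (1 − 0.20) = 15 per arm, 30 in total. This reproduces. The 12 per arm is a recommended minimum for a preliminary study, so there is no power calculation to reproduce.

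**Precision.**

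1. Per-patient variance of the change score: 2(1 − r).
2. Residual variance after regression on baseline: 1 − r².
3. Large-sample ratio, ANCOVA to change score: (1 − r²) / [2(1 − r)] = (1 + r)/2.
4. Penalty for estimating the slope with N = 24: 1 + 1/(N − 4) = 1.05.
5. 95% half-width: t × √(variance × 2/12), with t = 2.074 on 22 df for the t test and 2.080 on 21 df for ANCOVA. The 1.05 is included in the ANCOVA variance.

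**Imbalance.** The difference in mean baseline TNSS between arms has SD √(2/12) = 0.41. The chance that it exceeds 0.5 SD in either direction is 2[1 − Φ(0.5/0.408)] = 0.22. At 15 per arm the SD is √(2/15) = 0.37 and the chance is 0.17. Given an observed baseline difference d, the expected difference in change is the true effect minus (1 − r)d. For d = 0.5 the shift is therefore 0.5(1 − r).

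| r | (1 + r)/2 | × 1.05 | Half-width, change score | Half-width, ANCOVA | CI narrower by | Shift at 0.5 SD imbalance |
|---|---|---|---|---|---|---|
| 0.3 | 0.65 | 0.68 | 1.00 | 0.83 | 17% | 0.35 |
| 0.5 | 0.75 | 0.79 | 0.85 | 0.75 | 11% | 0.25 |
| 0.7 | 0.85 | 0.89 | 0.66 | 0.62 | 5% | 0.15 |
| 0.8 | 0.90 | 0.95 | 0.54 | 0.52 | 2.5% | 0.10 |
| 0.9 | 0.95 | 1.00 | 0.38 | 0.38 | none | 0.05 |

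**Check by simulation.** With 10,000 simulated trials at 12 per arm for each r, the variance ratios were 0.68, 0.79 and 0.89 at r = 0.3, 0.5 and 0.7. The mean CI width ratios were 0.83, 0.89 and 0.95. Both agree with the formulas.

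**The case against.** The case for leaving the plan alone has real content.

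- **Baseline is already used.** A reader might infer that baseline TNSS serves only for the between-arm significance test. It does not, because it enters every patient's change score. The fair comparison is change score against ANCOVA, and the table makes only that comparison.
- **A mixed model is also planned.** A reader might infer that unadjusted t tests are the whole plan and that nothing in it could correct an imbalance. The document does not support that. The mixed model may carry baseline, and an article may leave its covariates to the full protocol or SAP, so that silence is not a fault. But section 2.11 assigns this model to the search for significant differences and places the noninferiority interval next to the t test. Nothing stated makes the mixed model the source of that interval.
- **The t test is valid.** This stands. Over repeated randomisations the change-score difference is unbiased. The issue is lost precision and a shift conditional on the imbalance that occurred.
- **The baseline tests decide nothing.** This also stands. One might infer that an imbalance which passes the test is thereby cleared for analysis. A 0.5 SD difference would indeed pass (0.5/0.408 = 1.22 on 22 df, p about 0.23), but section 2.11 attaches no rule to the result. The tests are uninformative after randomisation but do not alter the estimate.
- **The gain may be small.** TNSS is recorded daily. If baseline and week-2 values are averages over several days, r could lie at the upper end of the range, where little is gained.
- **It is a feasibility trial.** The recruitment, completion and compliance measures in section 2.7 are untouched, and no hypothesis is powered. Yet section 2.11 states a noninferiority decision on a CI, so its width and position do matter.

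**Conclusion.** The point holds as a moderate, inexpensive improvement to a stated method. It does not make the planned comparison invalid. At 12 per arm, adjusting for baseline TNSS would narrow the 95% CI by about 17%, 11% or 5% at assumed correlations of 0.3, 0.5 or 0.7. It would also remove the conditional shift of 0.35, 0.25 or 0.15 SD that a 0.5 SD imbalance produces. The precision gain is about 2.5% at 0.8 and nil at 0.9. These figures rest on equal SDs and on correlations that the document does not supply. The article gives no value for the noninferiority margin, so the effect on that decision cannot be expressed relative to it.

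**What to change.** In section 2.11:

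1. Name one baseline-adjusted model as the source of both the primary estimate and the noninferiority 95% CI. It can be ANCOVA of week-2 TNSS (or change) on arm and baseline TNSS, or the mixed model with baseline TNSS as a covariate and the week-2 contrast as the estimate. State which one is primary.
2. Analyse the continuous secondary outcomes in the same way, each adjusted for its own baseline value. Section 2.6.2 already schedules screening measurements of the mini-RQLQ and total IgE, and a Nasal Endoscopy Index at randomisation.
3. Remove the between-arm significance tests on baseline variables and keep the descriptive baseline table.

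The cost is a change of wording and one degree of freedom per model. No new data, visits or patients are needed.

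### One-sided t tests of unstated level sit under a two-tailed 0.05 rule, and a mixed model tests the same differences again with no role given to the t test

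*Protocol article*

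**What the plan says.** Section 2.11 (Statistical analysis) of the protocol article makes four statements about the comparison of the two groups.

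- On the outcomes in general: "Differences in the primary and secondary outcomes will be analyzed using one-sided independent" *t* tests. No level is attached to these tests.
- On noninferiority, for the primary outcome only, the interval is held against a margin: "we will check whether the lower limit of the 2-sided 95% CI of the difference of the primary outcome between the 2 groups" lies above it.
- On difference, a further analysis of the same outcomes is meant to settle whether the groups differ significantly: "differences in the primary and secondary outcomes will be analyzed using a mixed effects model for repeated measurement".
- On the level for the whole section: "The level of significance will be set at 0.05 (2-tailed").

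The abstract fixes the endpoint: "The primary outcome will be the mean change in the total nasal symptom score from baseline to week 2". Section 2.6.1 adds that the TNSS scores from all 4 weeks will be used to compare the two drugs and the duration of their effects. Section 2.10 takes the sample size from a pilot-study recommendation of "12 subjects in each group, for 24 subjects in total", raised to 15 per group for dropout.

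**The concern.** A one-sided test cannot be judged at a two-tailed 0.05 level unless its own level is given. One-sided 0.025 would agree with the two-tailed rule; one-sided 0.05 would not. The article does not choose. A result could then be called significant by the *t* test while the promised 95% CI includes zero.

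The second difficulty is that two procedures address the group difference in the same outcomes. The mixed model has a stated purpose; the *t* test has none. They need not agree even at matching levels, because the *t* test would use the change to week 2 and a repeated-measures model may draw on all 4 weeks. If either may be cited, the chance of a false claim exceeds that of one prespecified test, and the favourable result can be chosen afterwards.

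This matters more than usual here because the trial is open label, the primary outcome is recorded by the patients, and the findings are meant to support a full-scale trial (sections 2.6.1, 2.9 and 3).

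**Working it through.** **Inputs from the article.** Two-tailed 0.05 level, one-sided *t* test of unstated level, two-sided 95% CI rule and mixed model (section 2.11); 12 evaluable per group, 20% dropout, 15 recruited per group (section 2.10); primary endpoint at week 2 (abstract). The article gives no SD and no correlation between visits, so these are assumed below.

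**Step 1: the plan's own figure.** 12 / (1 − 0.20) = 15 per group, 30 in total. This reproduces. The calculation uses no alpha, power or margin, so the sample size does not show which level was intended.

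**Step 2: cut-offs.** Degrees of freedom are 2n − 2.

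| n per group | df | one-sided 0.05 | one-sided 0.025 = two-sided 0.05 |
|---|---|---|---|
| 12 | 22 | 1.717 | 2.074 |
| 15 | 28 | 1.701 | 2.048 |

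A one-sided 0.05 cut-off corresponds to a two-sided p of 0.10. A *t* between the two columns, in SCRT's favour, passes one rule and fails the other.

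**Step 3: width of that window.** The standardised difference is t × √(2/n).

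- n = 12: 1.717 × 0.408 = 0.70 SD to 2.074 × 0.408 = 0.85 SD.
- n = 15: 1.701 × 0.365 = 0.62 SD to 2.048 × 0.365 = 0.75 SD.

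The chance of falling in the window is 0.05 − 0.025 = 2.5% with no true effect. From the noncentral *t*, at a true difference of 0.5 SD, it is 10.8% (n = 12) or 11.7% (n = 15).

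**Step 4: null error if either result counts, one statistic.** One-sided 0.05 in SCRT's favour plus the 0.025 tail against it gives 0.05 + 0.025 = 7.5%.

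**Step 5: null error if either the *t* test or the mixed model counts.** This was simulated with no treatment effect. The *t* test is on the change to week 2, and the mixed model is approximated by a two-sided 0.05 test of one contrast. The first four rows use 100,000 trials per setting, 12 and 15 per group, and equal correlations of 0.3, 0.5 and 0.7 between baseline, week 2 and week 4. The last row uses 20,000 trials, 15 per group and correlation 0.6 between weekly scores.

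| *t* test level | model contrast | any direction | favouring SCRT |
|---|---|---|---|
| one-sided 0.05 | change averaged over weeks 2 and 4 | 8.0–8.3% | 5.6–5.8% |
| one-sided 0.05 | baseline-adjusted week 2 | 8.0–8.4% | 5.5–5.8% |
| one-sided 0.025 | change averaged over weeks 2 and 4 | 6.1–6.3% | 3.6–3.8% |
| one-sided 0.025 | baseline-adjusted week 2 | 5.9–6.4% | 3.4–3.8% |
| one-sided 0.05 | baseline-adjusted mean of 4 weeks | 9.1% | 6.6% |

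The reference values for one two-sided 0.05 test are 5% and 2.5%. Setting the *t* test to 0.025 removes the sidedness conflict, but the excess goes only when one test of difference decides.

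**Step 6: the noninferiority rule.** The lower limit of a two-sided 95% CI set against a margin is a one-sided 0.025 test, which agrees with a two-tailed 0.05 level. Its null hypothesis concerns the margin, not zero.

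**The case against.** The best defence is that the one-sided *t* test is the noninferiority test, run at 0.025, and the mixed model is the only test of difference. The neighbouring sentence on the 95% CI allows this, and the rates would then be 2.5% for noninferiority and 5% for difference. It fails as a full answer because the noninferiority rule covers only the primary outcome, while the one-sided *t* tests also cover the secondary outcomes, for which no noninferiority rule is given. It does show that the level of the *t* test is unstated rather than known to be 0.05.

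Three stronger readings are therefore tempting but unsupported.

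- A reader might infer that the trial's error rate is not 5%, or that the chance of a false claim for SCRT is doubled. Both require the one-sided test to be run at 0.05, which the article does not say.
- A reader might count the CI rule as a third competing analysis. The article gives separate purposes to the CI rule and the mixed model, and a noninferiority test followed by a test of difference does not in itself inflate error. Only the role of the *t* test is unclear.
- A reader might take 9.1% as the size of the problem. That figure averages in the 2 weeks after medication stops, whereas the primary endpoint is at week 2; it is the top of a range.

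It is also fair that this is a feasibility trial whose sample size uses no alpha, so the practical harm is limited. The direction of each one-sided secondary test is a detail that an article may leave to the full protocol or SAP, and is not held against it here. None of this reconciles the sentences in section 2.11.

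**Conclusion.** The point holds in limited form. Section 2.11 contradicts itself on sidedness and leaves the *t* test without a role beside a mixed model that tests the same differences; nothing elsewhere in the article settles either matter.

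The size is conditional. The window of conflicting results exists only if the one-sided test is run at 0.05. The either-test error of about 8–9% (about 5.5–6.6% favouring SCRT) further requires that either result may support a claim. With the *t* test at 0.025, that second condition alone leaves about 6% (3.4–3.8% favouring SCRT). The simulated rates also depend on the assumed correlations and on the approximation of the mixed model by a single contrast.

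**What to change.** In section 2.11 and the SAP:

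1. Delete the one-sided *t* tests of difference, or make them two-sided at 0.05 (equivalently, state one-sided 0.025).
2. Keep the two-sided 95% CI rule for noninferiority of the primary outcome.
3. Name the mixed-model treatment difference in TNSS change from baseline to week 2, two-sided 0.05 with its 95% CI, as the one deciding test of difference.
4. Label any retained *t* tests, and all tests of secondary outcomes, as supportive.

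The cost is wording only. The downside is a slightly stricter threshold for SCRT than a one-sided 0.05 test would give: 2.07 rather than 1.72 at 22 df. Making the test of difference the sole primary analysis would go too far. It would demote the planned noninferiority comparison, which bears on the article's stated question of whether SCRT could be an alternative to conventional therapy (section 3).

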### Data management

2.12

Monitoring will be conducted to control the quality of data and to protect the rights of participants. According to the planned protocol and standard operating procedures, monitors will evaluate whether the recruitment procedures are correctly performed and whether the data are adequately recorded. All data and records related to the clinical trials will be kept in a locked cabinet. Documents related to clinical trials should be kept for 10 years after completion of the clinical trial under the supervision of the custodian after completion of the clinical trial result report.

### Safety and adverse events

2.13

For observation of the safety of study participants, serum complete blood cell count tests, liver and kidney function tests, and urine analysis will be performed at the screening visit, at the completion of medication and at follow-up 2 weeks after completion of medication. Contact information will be provided to all participants for reporting of adverse events at any time. Investigators will also check vital signs and any expected or unexpected adverse events at every visit. Any adverse events will be reported in accordance with the guidelines of the Institutional Review Board.

### Ethics

2.14

This study complies with the principles of the Declaration of Helsinki and Good Clinical Practice guidelines. This research protocol has been reviewed and approved by the Institutional Review Board of the Woosuk Korean Medicine Hospital of Woosuk University (WSOH IRB D1705-020-1). This study is registered with the national clinical trial registry Clinical Research Information Service, which is a primary registry of the World Health Organization International Clinical Trials Registry Platform (http://apps.who.int/trialsearch/Trial2.aspx?TrialID=KCT0002380). Voluntary written informed consent will be obtained from all study participants prior to enrolment in the study. If a participant is injured or if adverse drug reactions occur while participating in the study, the subject will be financially compensated under the terms of the insurance contract and the clinical trial center for this study. The knowledge generated from this study will be shared with health care professionals, the general public, traditional medicine associations, and other relevant organizations through manuscript publication, conference presentations, and seminars.

## Discussion

3

This study is a feasibility trial to assess the safety and clinical effectiveness of SCRT in AR patients who are not well-controlled by conventional therapies.

In this study, we will enroll patients with a history of at least 2 years of persistent AR. The 2 year criterion was chosen based on the inclusion criteria of previous studies of uncontrolled AR patients.^[31,32]^ The strict meaning of “uncontrolled” can be “persistence of severe symptoms,” but in this study we interpreted it as, “the symptom frequently occurs despite steady treatment.” As in previous studies, we considered that 2 years of AR history is long enough to assess the success of conventional therapies. Thus, patients with a history of at least 2 years of persistent AR form the target population in this study.

This study was designed to refine treatment regimen of SCRT, and to evaluate whether SCRT could be an alternative to conventional therapy. In East Asia, SCRT has been used for the treatment of respiratory diseases such as the common cold, asthma, and allergic rhinitis, and studies are being conducted to evaluate its effectiveness.^[20,33,34]^ In this study, we apply cold–heat pattern identification diagnosis, which is a basic diagnostic tool for Korean Medicine.^[35]^ SCRT showed more effectiveness in relieving common cold symptoms in patients who had a cold pattern than in patients who had a hot pattern.^[33]^ Thus, we assume that the effect of SCRT will be different according to cold and heat pattern. By subgroup analysis of cold–heat pattern, we can draw conclusions about the use of pattern identification for prescription of herbal medicine. In addition, we will report the changes of each symptom of allergic rhinitis to find possible indications for SCRT as a complement to cetirizine.

In this study, blinding of the participants is impossible because of the use of different types of drugs (granules for SCRT and tablets for cetirizine). In pragmatic RCTs, although the participants and investigators are often un-blinded, it is still desirable and often possible to blind the assessors or to obtain an objective source of data for evaluation of outcomes.^[36]^ However, in the case of AR, the subjective symptoms of the patient are recommended as the primary outcome. In this study, serum IgE and the Nasal Endoscopy Index, evaluated by 2 independent assessors, are added as a secondary variable to minimize bias.

The findings of this study are intended to provide the basis for a full-scale randomized controlled trial to confirm the safety and effectiveness of SCRT for the treatment of nasal symptoms in AR patients who was not controlled by conventional therapy.

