#### Secondary outcomes

2.6.2

Secondary outcomes include the mini Rhinoconjunctivitis Quality of Life Questionnaire (RQLQ) and total serum IgE, which will be measured 3 times in total, at screening and 2 and 4 weeks after randomization. The mini-RQLQ is an abbreviated form of the RQLQ, and consists of 14 questions about activities, behavioral problems, nose symptoms, eye symptoms, and other symptoms related to AR. Each item produces a score from 0 to 6 according to the severity of the symptoms.^[26,27]^

To evaluate the effects of SCRT on allergic and inflammatory reactions, we will examine differential white blood cell counts (neutrophil, eosinophil, basophil, monocyte, and lymphocyte) and conduct total serum IgE tests at 2 and 4 weeks after randomization.

To search for the more precise indication of using SCRT, we will use the Cold–Heat Pattern Identification Questionnaire and Nasal Endoscopy Index. The Cold–Heat Pattern Identification Questionnaire is used to distinguish between cold and heat, which is a characteristic of patients from a Korean traditional medicine perspective. The questionnaire consists of 15 symptom-based items, including 8 items related to cold and 7 items related to heat. According to the results of this questionnaire, a patient could be classified as Cold, Heat, neither Cold nor Heat and Cold–Heat complex.^[28]^ The Nasal Endoscopy Index will be used for supplementary evaluation of subjective symptoms of TNSS at the time of randomization and 1, 2, and 4 weeks after randomization. The instrument used is the KAZAMA ENT treatment unit (KAU-3000, HARMONY, ENT Co., Ltd., Incheon, Korea). The efficacy is assessed by scoring the status of the nasal cavity according to an assessment scale developed by Yun et al. It consists of 4 categories for the evaluation of color, dryness/dampness, nasal discharge, and atrophy/edema of the lower nasal turbinates, using a 3-point severity scale scored from normal (0), mild (1), to severe (2).^[29]^

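### The Discussion promises conclusions on prescribing by cold–heat pattern, but four patterns among 24 evaluable patients leave about three per arm per pattern, too few to support any

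*Protocol article*

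**What the plan says.** Section 2.11 (Statistical analysis) of the protocol article plans subgroup work: "Subgroup analyses will also be conducted to investigate the difference in treatment effect according to the type of" cold–heat pattern, each symptom of allergic rhinitis and the Nasal Endoscopy Index. Section 2.6.2 (Secondary outcomes) describes the questionnaire: "a patient could be classified as Cold, Heat, neither Cold nor Heat", with a mixed Cold–Heat class as the fourth.

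The Discussion states the authors' expectation that the effect of SCRT differs by pattern, and then what the analysis will deliver: "we can draw conclusions about the use of pattern identification for prescription of herbal medicine". Neither section calls the subgroup analysis exploratory.

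The sample comes from a rule of thumb for preliminary studies (section 2.10): "12 subjects in each group, for 24 subjects in total". After an allowance for dropout, "the target of the recruitment is set to 15 subjects in each group, or 30 subjects in total". Section 2.11 analyses randomized patients who complete the trial with complete data, so 24 is the planned number for analysis.

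**The concern.** The Discussion sentence is a positive claim about what the trial can show, so it is not a detail left to an analysis plan. Comparing the effect of SCRT with that of cetirizine across four patterns divides the sample into eight arm-by-pattern cells. The sample was not sized on power even for the main comparison, and the article describes no stratification by pattern.

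With cells this small, apparent differences between patterns would be mostly noise. Under the sentence as it stands, such a difference could be reported as a finding on how the herbal medicine should be prescribed. An absent difference could equally be reported as evidence against pattern identification. Neither inference would be sound. Section 2.14 (Ethics) foresees sharing the results with health care professionals and the public, so the strength of the claim matters.

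**Working it through.** **Inputs**
- Evaluable patients: 12 per arm, 24 in total (section 2.10).
- Dropout: 20% (section 2.10).
- Allocation: 1:1 (Abstract).
- Patterns: 4 (section 2.6.2).
- Two-sided significance level: 0.05 (section 2.11).
- SD of the outcome: not given, so results are in SD units.
- Prevalence of each pattern: not given. An even split is assumed first and then varied.

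**The plan's own figure.** 12 / (1 − 0.20) = 15 per arm, 30 in total. This reproduces the stated target exactly.

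**Cell size.** 24 / (4 × 2) = 3 per arm per pattern. If all 30 were analysed, 30 / 8 = 3.75.

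**Treatment effect within one pattern, 3 per cell.** SE = √(2/3) = 0.816 SD.
- Variance pooled over all eight cells, df = 8 × (3 − 1) = 16: half-width = 2.120 × 0.816 = 1.73 SD.
- Only that pattern's six patients, df = 4: half-width = 2.776 × 0.816 = 2.27 SD.

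**Difference in treatment effect between two patterns (interaction).** SE = √(4/m), where m is the number per cell. Power is from the noncentral t distribution.

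| Case | m | df | SE (SD) | Power for 1 SD | Interaction detectable with 80% power |
|---|---|---|---|---|---|
| Two of four even patterns, e.g. Cold v Heat | 3 | 16 | 1.155 | 13% | 3.45 SD |
| As above, cell rounded up for all 30 analysed | 4 | 24 | 1.000 | 16% | 2.92 SD |
| Only two patterns occur, equal size | 6 | 20 | 0.816 | 21% | 2.4 SD |
| As above, cell rounded down for all 30 analysed | 7 | 24 | 0.756 | 25% | 2.21 SD |

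**Size needed.** With the normal approximation, a 1 SD interaction between two patterns at 80% power needs 4 × (1.960 + 0.842)² / 1² = 31.4, so 32 per cell, or 4 × 32 = 128 patients in those two patterns alone.

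**Sparse cells.** This was a simulation with 12 patients per arm and pattern falling at random.

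| Assumed prevalence of the four patterns | At least one of 8 cells empty | At least one cell with 0 or 1 patient |
|---|---|---|
| 25/25/25/25% | 23% | 81% |
| 40/20/25/15% | 42% | 93% |
| 50/15/20/15% | 55% | 97% |

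The even split is therefore the most favourable of these for filling all the cells.

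**The case against.** The best defence is that this is one sentence in the Discussion of a study described throughout as a feasibility trial. Section 2.6.2 speaks only of searching for a more precise indication, the Discussion itself speaks of possible indications, and its close leaves confirmation to a full-scale trial. An underpowered exploratory subgroup analysis in such a trial is not an error. That stands: the analysis may stay, and the fault lies in the inference attached to it. The softer wording nearby does not cancel an unhedged statement that conclusions can be drawn.

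Three stronger readings are tempting, and the article does not support them.
- A reader might infer that the endoscopy subgroup will be formed on values taken after treatment began, which would undermine the randomized comparison. The index is measured "at the time of randomization and 1, 2, and 4 weeks after randomization", so a baseline value exists. Section 2.11 does not say which visit is used, and an analysis plan that is not shown could settle it.
- A reader might infer that the symptom analyses are mis-specified because section 2.11 lists symptoms among the subgroups. The Discussion says that changes in each symptom will be reported, which is outcome reporting. The label is loose, but no wrong analysis follows.
- A reader might infer that chance pattern differences will set the entry criteria of the full-scale trial. The article says no such thing. It describes that trial's population as patients not controlled by conventional therapy, with no pattern criterion.

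**Conclusion.** The concern holds for the stated inference. With 24 evaluable patients and four evenly spread patterns, the effect within a pattern is known only to within about 1.7 to 2.3 SD either way. Power for a 1 SD interaction is about 13% for two of the four patterns, and about 21% if only two equal patterns occur. Analysing all 30 does not change the picture.

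The figures rest on an assumed even split, a common SD across cells and results in SD units. An uneven split makes the smallest cells smaller still. The point is about what the trial may conclude. It does not invalidate the design, and the timing of the endoscopy value and the listing of symptoms are matters of clarification only.

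**What to change.** In the Discussion, replace the sentence on drawing conclusions with a statement that the cold–heat analysis is exploratory and hypothesis-generating. Add the same label in section 2.11. Report the number of patients per arm in each pattern and the treatment-by-pattern interaction estimate with its 95% confidence interval, with no significance claim and no statement on prescribing. Where a cell is empty, say that the contrast cannot be estimated.

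As a secondary clarification in section 2.11: if the Nasal Endoscopy Index is used as a modifier, name its value at randomization, and describe the individual symptom scores as components of the outcome rather than as subgroups.

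No extra patients, visits or measurements are needed. The cost is a few changed sentences, an interaction estimate in the report and a weaker claim about pattern identification.
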